### Stereotactic Body Radiotherapy

SBRT will be delivered in an image-guided hypofractionated scheme of 60 Gy in 3, 5 or 8 fractions, prescribed to 95% of the planning target volume (PTV). The 5 or 8 fraction schedule will be used in case of overlap with central hilar structures, large vessels, gallbladder or in cases where under-dosing the gross tumour volume (GTV)/PTV is necessary due to near critical structures (oesophagus, stomach, duodenum, bowel). In preparation for treatment delivery, all patients will undergo a planning-CT scan or a planning MRI in case of MR guided treatment. Abdominal compression, gated treatment or breath hold may be used, but is not mandatory. Intravenous contrast may be used during simulation; however, it is not required. Fusion will be centred on the area of interest i.e. the CRLM. The PTV will be generated with the addition of a 3–10 mm margin around the gross tumour volume (GTV) depending on institutional protocols. The duodenum, stomach, bowel, liver, kidneys, and spinal cord will be contoured as avoidance structures. Other tissue structures will be contoured depending on the method of motion management. When an internal target volume (ITV) concept is used including motion, motion should also be included in the delineation of critical structures for maximum critical dose (i.e. oesophagus, stomach, bowel, duodenum). The liver should be delineated on the average phase bin and not include all motion, otherwise the volume of low liver dose will be overestimated. Radiation therapy will be delivered using any high-precision SBRT technique; this can be in the form of MR guided radiotherapy, intensity-modulated radiotherapy (IMRT), volumetric modulated arc therapy (VMAT), tomotherapy, or using multiple non-coplanar fields or arcs. If disease recurrence is detected and treated with re-SBRT within 6 months after the initial treatment the radiation-site recurrence will not be regarded as an event for the primary endpoint. Re-SBRT will have to be performed with sufficiently high doses to be considered ablative.

### Follow-Up

Follow-up imaging and laboratory tests will be identical in both treatment arms to avoid bias with regards to both the primary and secondary endpoints such as distant progression (Fig. 2). Patients will be asked to complete quality of life questionnaires at baseline and every 3 months for the first year. All potential LTPs will be reviewed by an expert panel including independent abdominal radiologists in presence of the study PI’s.

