### Statistics

Given the unknown 1 year LTP rate for intermediate-size CRLM for both techniques, it was not possible to apply validated assumptions for both proportions. Hence a difference in 1y-LTP rate of more than one third (33%) is considered clinically relevant as it seems unlikely that a smaller difference will significantly impact overall survival. Most 1-year LTP will either be re-ablated or patients will receive systemic chemotherapy because of the simultaneous presence of extensive distant progression. In other words, unablatable LTP at 1-year without recurrence at distant sites is uncommon. We therefore accept that a difference in 1 year LTPFS of more than one third (0.33) will reject the null hypothesis concluding that the techniques are significantly different [17]. Group sample sizes of 33 in group 1 and 33 in group 2 achieve 81.059% power to detect a difference between the group proportions of −0.33. The proportion in group 1 (the treatment group) is assumed to be 0.665 under the null hypothesis and 0.3350 under the alternative hypothesis. The proportion in group 2 (the alternative treatment group) is 0.665. The test statistic used is the two-sided Z-test with un-pooled variance. The significance level of the test is 0.05. To account for a 3% loss to follow-up (= 2 patients) we need to randomize 34 patients (NR) into each of the two arms.

Baseline patient-, tumour- and treatment characteristics will be described and compared between the two treatment arms using the Chi-square test for categorical variables and the independent two-sample t-test, ANOVA or Mann–Whitney-U-test for continuous variables. *P* values below 0.05 will be considered significant. When appropriate, box-plots and cross-tables will be used for descriptive statistics of continuous and categorical variables, respectively. One year LTPFS rates will be compared between MWA and SBRT using the Chi square test. To determine hazard ratios (HR) for multivariate analysis, logistic regression will be used. Univariate LTPFS time analysis will be performed using the Kaplan–Meier method with corresponding two sided 95% confidence intervals (CI). Differences in LTPFS length will be analysed using the log rank test.

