### Study Cohort

Patients eligible for percutaneous ablation will be randomized prior to the procedure into one of two study arms: percutaneous MWA (arm A) or SBRT (arm B). Patients with at least one additional CRLM requiring resection will undergo laparoscopy or laparotomy with surgical inspection of the abdominal cavity and intraoperative ultrasound (IOUS) and if still considered eligible randomized intraoperatively. If randomized to MWA during open laparotomy, the eligible tumours will be ablated in the same procedure using ultrasound guidance. Patients included in study arm B will undergo SBRT at a later time. SBRT will be planned as soon as the patient is recovered from surgery. Patients randomized prior to treatment will have to be treated within 4 weeks after randomization.

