### Microwave Ablation

MWA procedures will be performed by a board certified operator striving for a tumour free ablation margin of at least 1 cm, according to the CIRSE quality improvement guidelines [18]. Contra -indications for a percutaneous approach are proximity of critical structures that cannot be distanced using pneumo- or hydrodissections. The interventional radiologist will assess the necessity for overlapping re-ablations and needle repositioning. To assess technical efficacy a ceCT (or ceMRI) should be made within two weeks after the procedure. Completion ablations for residual disease or inadequate tumour-free safety margins are allowed if detected on cross-sectional imaging and retreated ≤ 6 weeks after initial treatment. In this case, the initial procedure will be evaluated as a technically unsuccessful procedure. However, when successfully re-ablated the retreated residue will not count as an event for the primary endpoint LTPFS. If successfully re-ablated within 6 months after the initial treatment, early ablation site recurrence will not be regarded as an event for the primary endpoint 1 year LTPFS. The use of either rigid and/or non-rigid confirmation software is considered mandatory aiming at a minimum of 5 mm margins.

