### Outcome Measures

The primary objective is to compare 1-year local tumour progression free survival (LTPFS) from randomisation per treated tumour in both study arms. The 1 year LTPFS is defined as the percentage of successfully eradicated tumours 12 months following treatment, according to the RECIST and PERCIST criteria with a standardised follow-up protocol. LTP successfully retreated within the first 6 months, using the same technique as the initial treatment (re-MWA or re-SBRT) will not be regarded as an event for the primary endpoint. Secondary endpoints are: OS, local control (allowing repeat treatments with the same technique) overall and distant progression-free survival (DPFS), rate of adverse events and serious adverse events, quality of life assessments using EORCT QLQ-C30, EQ-5D, and PRODISQ questionnaires prior to, and 2 weeks, 3, 6, 9 and 12 months after local treatment.

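### Potential local progressions, the events of the primary endpoint, are reviewed with the principal investigators present, an avoidable exposure to assessment bias

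*Protocol article*

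**What the plan says.** The Follow-Up section of the protocol article describes how events are confirmed: "All potential LTPs will be reviewed by an expert panel including independent abdominal radiologists in presence of the study" principal investigators. Earlier in the same paragraph it gives its bias control: "Follow-up imaging and laboratory tests will be identical in both treatment arms to avoid bias with regards to both the primary and secondary endpoints".

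Outcome Measures shows what the panel's calls feed into: "The primary objective is to compare 1-year local tumour progression free survival (LTPFS) from randomisation per treated tumour in both study arms". Tumour status is to be read "according to the RECIST and PERCIST criteria with a standardised follow-up protocol".

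Event status can also depend on a retreatment. Outcome Measures exempts some progressions: "LTP successfully retreated within the first 6 months, using the same technique as the initial treatment (re-MWA or re-SBRT) will not be regarded"; these drop out of the event count for the primary endpoint. The Microwave Ablation section has a similar rule for residual disease: "when successfully re-ablated the retreated residue will not count as an event for the primary endpoint LTPFS". Neither section says who judges that success.

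The article nowhere says that the principal investigators have no vote, that the independent radiologists read first, or that clinical information is withheld from the panel.

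**The concern.** LTP in an ablated or irradiated area is a reading of images, not a hard event such as death. The term open-label does not appear in the article, but MWA and SBRT cannot be hidden from the people who run the trial, so the principal investigators can know each patient's arm. An independent panel is used so that the event call does not depend on such knowledge. If investigators who know the allocation attend while the call is made, their knowledge and views can reach the readers, even without intent.

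At stake is the treatment comparison on the primary endpoint. If doubtful lesions were confirmed more readily in one arm than in the other, the difference in 1-year LTPFS would carry that tendency along with any treatment effect, and no later analysis could separate the two.

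**Working it through.** **Setting the text side by side**

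1. What is adjudicated: potential LTPs (Follow-Up). These are the events of the primary endpoint (Outcome Measures).
2. Who is there: a panel that includes independent abdominal radiologists, with the principal investigators (Follow-Up).
3. What the investigators can know: the arm, because the treatments are MWA and SBRT (Study Cohort).
4. What limits their influence: nothing stated. The identical follow-up schedule governs when and how patients are scanned, not who is in the room when the scan is judged.

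Items 1 to 4 establish exposure. They do not establish that bias occurs.

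**The plan's own figure**

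Inputs from Statistics: 33 per group, proportions 0.335 and 0.665, two-sided alpha 0.05, Z-test with unpooled variance.

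- Standard error = √[(0.335 × 0.665 + 0.665 × 0.335)/33] = √(0.44555/33) = 0.1162
- Power = Φ(0.33/0.1162 − 1.960) = Φ(0.880) = 0.8106

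This agrees with the stated 81.059%. Who attends the panel does not enter the calculation, so a change there leaves sample size and power as they are.

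**Weight of a single call**

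- Per patient, 33 per arm: 1/33 = 0.030, about 3 percentage points; 2/33 = 0.061, about 6 points.
- Per tumour: with 1 to 3 target tumours per patient (Inclusion Criteria), an arm holds between 33 and 99 target tumours. One lesion then moves the rate by between 1/99 = 0.010 and 1/33 = 0.030. Three points is the upper end.

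**What one-sided misreading could do (illustration; m is assumed)**

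Let both arms have the same true LTP rate p, and let a share m of true LTPs go unconfirmed in one arm only, so that its observed rate is p(1 − m). With 33 patients per arm and one observation each, the exact probability that the two-sided unpooled Z-test rejects is:

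| p | m = 0 | m = 10% | m = 20% | m = 30% |
|---|---|---|---|---|
| 0.335 | 5.4% | 6.4% | 9.6% | 15.5% |
| 0.665 | 5.4% | 9.5% | 21.8% | 41.2% |

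The values of p are the two planning proportions, taken here as LTP rates. No value of m can be obtained from the document. The table shows only that the error rate responds to one-sided misreading, not that such misreading is expected.

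**The case against.** The strongest reply is that presence is not participation. The article does not say that the investigators vote, present the clinical course or speak before the read. Voting rules and read order are details that a condensed article may leave to the full protocol or a panel charter, neither of which is shown. This stands in part: a reader might infer that the panel's independence is lost, and the text does not support that. But the attendance itself is stated, not omitted, and nothing shown qualifies it.

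Three further inferences also go too far.

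- *That the investigators favour one result.* The article declares equipoise, seeks superiority of either technique and plans a two-sided test. No direction of bias can be named.
- *That the panel judges retreatment success with the investigators present.* Follow-Up gives the panel potential LTPs only. The retreatment rules do not mention the panel.
- *That the result hangs on one call.* By uncorrected chi-square, 12/33 against 20/33 gives p = 0.049 and 13/33 against 20/33 gives p = 0.085. Any small binary trial is this fragile at its threshold, whoever adjudicates. The example also depends on the version of the test (p = 0.085 with continuity correction and 0.084 by Fisher's exact test for 12/33 against 20/33), and it counts patients although the endpoint is per tumour.

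The existing safeguards deserve credit: independent radiologists on the panel, RECIST and PERCIST criteria, identical follow-up, and monitor verification of the primary outcome for every subject (Data Monitoring). They lower the risk. None of them governs who attends when a doubtful lesion is called, and checking the case report form against source data does not test the imaging judgement.

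**Conclusion.** The point holds as an avoidable exposure to assessment bias on the primary endpoint. It rests on one stated procedure and on one inference, that investigators in a trial of MWA against SBRT can know the arm. The document gives no basis for the size or direction of any bias. The only scale available is illustrative: about 3 percentage points for one reclassified patient of 33, and between about 1 and 3 points for one lesion. The point does not invalidate the design. It is worth acting on because the exposure is unnecessary and cheap to remove.

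**What to change.** Replace the sentence on panel review in Follow-Up with wording such as:

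*Each potential LTP is decided by the independent abdominal radiologists on the panel against the prespecified criteria, without the principal investigators present and without clinical notes or outcome data. The principal investigators supply only imaging and treatment dates beforehand and answer questions in writing.*

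If the success of a retreatment is also judged in order to settle event status, as the Microwave Ablation and Outcome Measures rules imply, assign that judgement to the same independent readers.

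The cost is a slightly slower review, because clinical questions go in writing. No extra readers are needed, and the imaging schedule, sample size and power stay as they are. The gain has two limits. Readers may still recognise the technique on the images, so full masking is not possible. And only potential LTPs are said to reach the panel, so the first read that flags a scan remains outside this safeguard.

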**Fig. 2 Fig2:**
[figure not shown]
Follow-up

### Outcome Measures

The primary objective is to compare 1-year local tumour progression free survival (LTPFS) from randomisation per treated tumour in both study arms. The 1 year LTPFS is defined as the percentage of successfully eradicated tumours 12 months following treatment, according to the RECIST and PERCIST criteria with a standardised follow-up protocol. LTP successfully retreated within the first 6 months, using the same technique as the initial treatment (re-MWA or re-SBRT) will not be regarded as an event for the primary endpoint. Secondary endpoints are: OS, local control (allowing repeat treatments with the same technique) overall and distant progression-free survival (DPFS), rate of adverse events and serious adverse events, quality of life assessments using EORCT QLQ-C30, EQ-5D, and PRODISQ questionnaires prior to, and 2 weeks, 3, 6, 9 and 12 months after local treatment.

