### Inclusion Criteria

Patients with 1–3 unresectable intermediate-size CRLM, suitable for both MWA and SBRT are eligible to participate. An overview of inclusion and exclusion criteria is listed in Table 1. Additional CRLM are allowed if they are either resectable or < 3 cm and amenable for thermal ablation. In total, a maximum of 10 CRLM without extrahepatic disease or 5 CRLM in case of limited extrahepatic disease is allowed. Prior focal liver treatment is allowed, but resection or ablation site recurrences are disqualified as target lesions. Patients without prior focal liver treatment should be either unsuitable for 1st line systemic therapy or have progressed under/after 1st-line systemic therapy. Potential candidates will be registered and undergo routine pre-procedural work-up: baseline full blood examination, ceCT of the chest and abdomen and either an upper abdominal ceMRI or a total body ^18^F-FDG PET-CT.

**Table 1 Tab1:** Inclusion and exclusion criteria

Inclusion criteria	Exclusion criteria
Histological documentation of primary colorectal tumour	No target lesions suitable for both ablation and SBRT
Age > 18 years	Chemotherapy ≤ 6 weeks prior to the procedure
1–3 unresectable CRLM size 3–5 cm eligible for both MWA and SBRT (target lesions)	Immunotherapy ≤ 6 weeks prior to the procedure
Additional CRLM are allowed if considered either resectable, or ablatable and < 3 cm	Severe allergy to contrast media not controlled with premedication
No or limited extrahepatic disease (1 extrahepatic lesion is allowed, not including positive para-aortal lymph nodes, celiac lymph nodes, adrenal metastases, pleural carcinomatosis or peritoneal carcinomatosis)	Compromised liver function (e.g. signs of portal hypertension, INR > 1,5 without use of anticoagulants, ascites)
For subjects with liver only disease the maximum number of CRLM is 10; for subjects with limited extrahepatic disease the maximum number of CRLM is 5	Radical treatment unfeasible or unsafe (e.g. insufficient future liver remnant [FLR])
Resection for additional resectable lesions is allowed when considered possible obtaining negative resection margins (R0) and preserving adequate future liver remnant	Pregnant or breast-feeding subjects
Prior focal liver treatment is allowed, but resection or ablation site recurrences are disqualified as target lesions	
Unsuitable for (further) systemic therapy	
Written informed consent	

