### Randomization

Blocked randomization with randomly selected block sizes of 4 and 6 will be performed centrally through a web-based module (CASTOR), with stratification according to presence of extrahepatic disease and patients undergoing surgical resection. According to the intention-to-treat concept, during statistical analysis all randomized patients will be analysed in the group they were originally assigned to even when receiving a different treatment.

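### The primary endpoint counts tumours, but randomisation and sample size count patients and the named test is an ordinary chi-square, so the 5% error rate may not be held

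*Protocol article*

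**What the plan says.** **Unit of the endpoint.** Outcome Measures places the primary objective on tumours ("LTPFS) from randomisation per treated tumour in both study arms") and repeats this in the definition, where the 1-year rate is "defined as the percentage of successfully eradicated tumours 12 months following treatment". The denominator is tumours both times.

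**Tumours per patient.** Table 1, under Inclusion Criteria, admits "1–3 unresectable CRLM size 3–5 cm eligible for both MWA and SBRT (target lesions"). Other lesions may be present and are handled separately: "Additional CRLM are allowed if they are either resectable or < 3 cm and amenable for thermal ablation".

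**Unit of randomisation and analysis set.** Both are patients. Under Randomization, "all randomized patients will be analysed in the group they were originally assigned to".

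**Sample size and test.** Statistics says "Group sample sizes of 33 in group 1 and 33 in group 2 achieve 81.059% power", with 34 patients randomised per arm after allowance for loss to follow-up. The comparison is stated without a unit: "One year LTPFS rates will be compared between MWA and SBRT using the Chi square test". The same section adds Kaplan–Meier estimates with 95% confidence intervals and a log-rank test, also without a unit. The article does not mention within-patient correlation, a clustered method or an index tumour.

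**The concern.** A Pearson chi-square is valid when the counted units are independent. Tumours in one patient share tumour biology, treatment session and usually operator, so their outcomes are likely to be positively correlated. If they are pooled as independent, the variance of the difference between arms is understated: p-values come out too small and confidence intervals too narrow. This is the single primary test of a 68-patient trial that aims to show one technique superior, so an inflated false-positive rate would bear directly on its conclusion.

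The article itself names both the unit and the test, and the two do not fit together. It is therefore not a detail left to an analysis plan or a fuller protocol.

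**Working it through.** **1. The plan's own figure.** Inputs from Statistics: rates 0.665 and 0.335, 33 per arm, two-sided 5%, Z-test with unpooled variance.

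- Variance sum: 2 × 0.665 × 0.335 = 0.44555
- Standard error: √(0.44555/33) = 0.1162
- Power: Φ(0.33/0.1162 − 1.960) = Φ(0.880) = 81.06%

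The stated 81.059% is reproduced with 33 independent observations per arm. One patient therefore counts as one observation, while the endpoint counts tumours.

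**2. True error of a per-tumour chi-square.** Let m be the number of target tumours per patient.

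- Design effect: DE = 1 + (E[m²]/E[m] − 1) × ICC
- True two-sided error: 2 × (1 − Φ(1.960/√DE))

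The document limits m to 1–3 but gives neither its distribution nor the ICC. Both are assumptions here.

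- 70/20/10% with 1/2/3 targets: E[m] = 1.40, E[m²] = 2.40, ratio 1.714
- 60/25/15%: E[m] = 1.55, E[m²] = 2.95, ratio 1.903
- 40/35/25%: E[m] = 1.85, E[m²] = 4.05, ratio 2.189

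| ICC | 70/20/10 | 60/25/15 | 40/35/25 |
|---|---|---|---|
| 0.05 | 5.4% | 5.5% | 5.7% |
| 0.1 | 5.8% | 6.0% | 6.4% |
| 0.2 | 6.7% | 7.1% | 7.8% |
| 0.3 | 7.5% | 8.2% | 9.2% |
| 0.5 | 9.3% | 10.4% | 12.1% |

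Example: 60/25/15 at ICC 0.3 gives DE = 1 + 0.903 × 0.3 = 1.271, then 1.960/√1.271 = 1.739, and an error of 8.2%.

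A simulation of the tumour-level test (33 patients per arm, true rate 0.665 in both, 40,000 runs per setting) gave 5.9%, 7.5% and 9.2% for the 70/20/10 mix at ICC 0.1, 0.3 and 0.5, in line with the formula.

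**3. Interval width.** The true standard error is √DE times the naive one. At ICC 0.5 that is √1.357 = 1.16 for 70/20/10 and √1.595 = 1.26 for 40/35/25.

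**4. Power of a clustered test.** The effective number per arm is 33 × E[m]/DE, taking 0.665 and 0.335 as per-tumour rates. At ICC 0.5:

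- 70/20/10: 46.2/1.357 = 34.0, power 82%
- 60/25/15: 51.15/1.452 = 35.2, power 84%
- 40/35/25: 61.05/1.595 = 38.3, power 86%

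These are large-sample figures. At ICC 0.7 with the 70/20/10 mix, power would be 78%.

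**The case against.** **The test may be meant per patient.** The chi-square sentence names no unit, the intention-to-treat statement speaks of patients, and the power calculation treats a patient as one observation. This reading is possible, and it is why the inflation is a consequence of one reading only. It does not clear the text: Outcome Measures defines the rate on tumours twice, and no patient-level event is defined for someone with two or three targets. On either reading the passages must be reconciled. For the same reason, the Kaplan–Meier intervals and the log-rank test share the flaw only if they are run per tumour.

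**The inflation may be small.** This is fair. It vanishes if the ICC is zero or every patient has one target, and for the 60/25/15 mix it is only 5.5–6.0% at ICC 0.05–0.1. A reader might infer that the 5% level is certainly broken. The document does not support that, because it gives neither quantity.

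**Non-target lesions.** Read literally, treated tumour could take in the additional resected or ablated lesions, and a reader might infer that the randomised contrast will be diluted. The rest of the document points the other way. The Introduction sets the comparison in unresectable 3–5 cm metastases, Inclusion Criteria separates target from non-target tumours, and Statistics frames the assumed rates on intermediate-size lesions. Outcome Measures also limits retreatment to repeat MWA or repeat SBRT, which does not fit a resected lesion. What remains is a loose word worth tightening.

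**Conclusion.** The concern holds as a mismatch between a tumour-level endpoint, patient-level randomisation and sizing, and a test that assumes independence. If the chi-square is run per tumour and outcomes within a patient are positively correlated, the nominal 5% is exceeded. Over the three assumed mixes, the excess runs from slight at ICC 0.1 or below to roughly double the nominal level at ICC 0.5.

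A reader might also infer that the trial is too small. That does not follow: for these mixes a clustered analysis keeps at least 82% power up to ICC 0.5. The exposure is in the primary p-value and interval. It should be corrected before analysis, because the choice of unit affects the result and should not be made with outcomes in view.

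**What to change.** Choose one unit and carry it through Outcome Measures and Statistics.

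- **(a) Tumour as unit.** Replace the plain chi-square with a test that treats the patient as cluster: a Donner-adjusted chi-square, or GEE with small-sample robust variance. Use patient-clustered variance for the Kaplan–Meier intervals and for the log-rank or Cox comparison.
- **(b) Patient as unit.** Define the event as progression of any target tumour, under the retreatment rules already stated, and keep the chi-square. This matches the randomisation and the existing power calculation. The 81.06% then applies only if 0.665 and 0.335 are patient-level rates.

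Under either option, state which unit the 0.665 and 0.335 refer to. As a clarification, write per target tumour in place of per treated tumour.

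The cost is protocol or analysis-plan wording. Option (a) also gives slightly wider intervals. No new data are needed, and under (a) the planned number of patients need not rise at the ICCs up to 0.5 and the mixes examined.

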**Methods:**

In this two-arm, multicentre phase II/ III randomized controlled trial, 68 patients with 1–3 unresectable, intermediate-size CRLM suitable for both MWA and SBRT, will be included. Patients will be treated with MWA or SBRT as randomised. The Primary endpoint is local tumour progression-free survival (LTPFS) at 1 year (intention-to-treat analysis). Main secondary endpoints are overall survival, overall and distant progression-free survival (DPFS), local control (LC) and procedural morbidity and mortality and assessment of pain and quality of life.

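### The primary endpoint has two start dates and counts only treated tumours, which conflicts with the promised intention-to-treat analysis; both problems differ by arm in patients randomised during surgery

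*Protocol article*

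**What the plan says.** All references are to the protocol article.

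- **Clock and unit, first sentence of Outcome Measures.** LTPFS at 1 year is compared "from randomisation per treated tumour in both study arms".
- **Clock and measure, next sentence.** "The 1 year LTPFS is defined as the percentage of successfully eradicated tumours 12 months following treatment".
- **Analysis set.** The abstract (Methods) states: "The Primary endpoint is local tumour progression-free survival (LTPFS) at 1 year (intention-to-treat analysis". The Randomization section states that "during statistical analysis all randomized patients will be analysed in the group they were originally assigned to even when receiving a different treatment".
- **Timing of treatment, Study Cohort.** Patients who need a resection as well are randomised in theatre. For MWA at open laparotomy, the ablation is done in that operation. For the other arm: "Patients included in study arm B will undergo SBRT at a later time". SBRT is planned once the patient has recovered, and no interval is given. A 4-week limit, the same for both arms, applies to patients randomised before treatment.
- **Retreatment windows, Microwave Ablation and Stereotactic Body Radiotherapy.** The 6-month windows within which a successfully retreated recurrence is not an event run from initial treatment in both arms.
- **Analysis, Statistics.** One-year rates are compared by chi-square, and LTPFS time by Kaplan-Meier and log-rank. The only allowance for missing outcomes is introduced by "To account for a 3% loss to follow-up (= 2 patients".

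**The concern.** Two adjacent sentences about the primary endpoint cannot both be followed. An analyst has to choose the start of the year, and nothing in the article prevents that choice from being made with the data in view.

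The denominator raises a separate problem. The intention-to-treat statement settles the case of a patient who receives the other treatment, since that tumour is still treated and stays in the assigned arm. It does not settle the case of a randomised patient whose target tumour is never treated. That patient has no treated tumour and drops out of a per-treated-tumour percentage.

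Neither problem is neutral between the arms for patients randomised in theatre. There the MWA interval is close to zero, while SBRT patients must first recover and may in that time progress, die or become unfit for treatment. Removing such patients is selection after randomisation.

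**Working it through.** **The plan's own figure.** Inputs from Statistics: 33 per group, proportions 0.335 and 0.665, two-sided Z-test with unpooled variance, alpha 0.05.

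- Standard error = √[(0.335×0.665 + 0.665×0.335)/33] = 0.116
- Power = Φ(0.33/0.116 − 1.96) = 81.06%

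This matches the stated 81.059%. The sample size is not in dispute here.

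**Effect of the clock.** Assume a constant hazard that begins at treatment, because local progression after treatment cannot occur before it. If S is LTPFS at 12 months from treatment and treatment comes g months after randomisation, LTPFS at 12 months from randomisation is S^((12−g)/12). The protocol gives no g for SBRT after surgery, so 2 and 3 months are assumptions. The 4-week row covers a reading in which the stated limit applies to everyone.

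| Delay | S = 0.665 | Shift |
|---|---|---|
| 4 weeks | 0.665^(48/52) = 0.686 | +2.1 points |
| 2 months | 0.665^(10/12) = 0.712 | +4.7 points |
| 3 months | 0.665^(9/12) = 0.736 | +7.1 points |

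These shifts apply to the delayed patients only. For the whole SBRT arm, multiply by the share having surgery, assumed to be 20-30%:

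- 0.20 × 4.7 = 0.9 points
- 0.30 × 7.1 = 2.1 points

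The direction is fixed: counting from randomisation flatters the arm treated later.

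**Effect of the denominator.** No untreated rate is given, so this is an illustration with one tumour per patient. Suppose 3, 6 or 10% of one arm (about 1, 2 or 3 of 34) are never treated and are counted as not eradicated instead of being dropped.

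- If that arm has the 0.665 rate, it becomes 0.665 × 0.97, 0.94 or 0.90 = 0.645, 0.625 or 0.599. The difference from 0.335 falls from 0.33 to 0.31, 0.29 or 0.26. Power by the formula above, with the new proportion in the variance, falls to 75.5, 69.3 or 60.4%.
- If that arm has the 0.335 rate, the difference widens. At 6%, 0.335 × 0.94 = 0.315, so the difference is 0.35.

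Counting untreated tumours as not eradicated therefore lowers the rate of the arm that has them. One patient in 33 is 3 points.

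**Deaths (secondary).** With 10% dying without local progression (assumed), 0.665 becomes 0.665 × 0.90 = 0.599 if death is an event, and 1 − 0.335 × 0.90 = 0.699 if such tumours count as progression-free.

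**The case against.** The strongest reply is that the imbalance is confined and small. Patients randomised before treatment have the same limit in both arms. Only the surgical stratum differs, and its size is not stated. A whole-arm shift of 0.9-2.1 points is minor beside a standard error of 11.6 points and a target difference of 33. This stands, and it limits the size of the clock problem. It does not remove the contradiction.

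A reader might go further in four ways that the document does not support.

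- **That the 4.7-7.1 points bias the whole comparison.** They belong to delayed surgical SBRT patients only.
- **That the clocks and the silence on deaths also breach intention to treat.** Only the treated-tumour denominator does. Either clock could be used with all randomised patients, given a rule for those never treated.
- **That untreated tumours will be much more common under SBRT.** A longer wait makes the direction plausible in the surgical stratum, but no rate is given.
- **That the missing rule for deaths is an error in its own right.** Censoring and event rules commonly sit in an analysis plan, which is not shown here, and the Kaplan-Meier and log-rank analyses can accommodate censoring. What remains is narrower: the endpoint is named survival, while its printed definition is only a percentage of tumours eradicated.

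The retreatment windows are not a source of inequality either, since they run from initial treatment in both arms.

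**Conclusion.** The point holds in a limited form. The primary endpoint contradicts itself on its start date, and its treated-tumour denominator conflicts with the promise to analyse all randomised patients. An unseen analysis plan does not excuse this, because the conflict lies in the printed definition.

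In patients randomised during surgery, both faults depend on arm. The clock moves the delayed patients' rate by about 4.7-7.1 points and the SBRT arm's by about 0.9-2.1 points. These figures rest on a constant post-treatment hazard, 66.5% 1-year LTPFS, a 2-3 month delay and a 20-30% surgical share. The last two are assumptions. The effect of the denominator cannot be sized from the document, but with 33 per arm one or two patients are enough to matter. The status of deaths is a secondary point of definition. The text should be corrected before analysis.

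**What to change.** 1. In Outcome Measures, start the year at randomisation, which fits the intention-to-treat promise.
2. Take as denominator all target tumours designated at randomisation, kept in the assigned arm. Count a target tumour that is never treated as not successfully eradicated; without such a rule it could pass as event-free.
3. Make the abstract, Statistics, Randomization and Outcome Measures agree with this.
4. State how the 6-month retreatment windows, which run from initial treatment, fit a clock that starts at randomisation.
5. Report the percentage at 12 months after treatment, in treated tumours, as a supportive analysis.
6. In the same definition, say whether death without local progression is an event.

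The cost is wording and a little programming, with no extra patients or visits. The downside is that delayed SBRT lesions have less post-treatment time at the 12-month landmark, by the amounts shown above. The supportive analysis makes that visible.
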